**Figure 1 F1:**
[figure not shown]
Stepped wedge design and participant timeline.

Secondary outcomes: Secondary outcomes will include: (i) percentage of pregnant women having their first antenatal visit before 13 weeks gestation; and (ii) mean birthweight.

Process measures include changes in empowerment for PWG members [measured using the validated Growth and Empowerment Measure (GEM)] (22), alongside a theory-generating process evaluation using qualitative methodology informed by Indigenist and critical theory of the implementation and experience of the intervention (42, 43).

A cost-consequence analysis (CCA) and cost-effectiveness analysis (CEA) will be undertaken from the health system perspective. The outcomes for the CCA will be all primary and secondary outcomes for the study. The outcome for the CEA will be a 100 g increase in mean birthweight (as the main direct health outcome measure).

### Participant Timeline

The non-randomized cluster stepped-wedge design involves staged implementation of the intervention with two services commencing the intervention planning period at three monthly intervals (Figure 1). Initially, the study was planned to be randomized in terms of the timing of commencement of the intervention, but it became apparent that some of the services were ready much earlier than their allotted start date, based on the pre-existence of a functional women's group. We considered stratified randomization, but ultimately came to the conclusion (with our service partners) that imposing a randomized order on a complex intervention with a presumed theoretical basis of empowerment was likely to be counterproductive in terms of relationship building/engagement with community members and was unpopular with staff at participating services. Thus, randomization of start order was abandoned, and time of commencement will be adjusted for statistically as part of the analysis.

The first phase of the study is the start-up phase and involves study set up, engagement of stakeholders, recruitment of services, recruitment of PWG facilitators, training and formation of PWGs. At the first service engagement meeting in late 2018, services were paired in terms of timing of the intervention for practical reasons based on geographic proximity, to improve feasibility of support (both from the project team and from facilitators at the partner site). The four “early ready” services will embark on the complex intervention first, at three month intervals. The remaining six services have agreed an order of implementation based on perceived readiness (Figure 1). On commencing the intervention, there is a 6-month intervention planning phase comprising the RSF Phase 1 planning workshops and between two and three years for the implementation of MCH improvement plans and monitoring implementation of planned changes (RSF Phase 2) depending on the time of entry.

### Sample Size

The study is conducted with ten services that have self-nominated and been engaged with MCH audits. The number of maternal records examined in a service at a single audit cycle ranges from <5 to >100, but is usually ~20. Actual mean of the MCH-QCI from 43 services previously involved with One21seventy MCH audits is 65.97% with standard deviation (SD) of 13.58% and a change of 5% is likely to be clinically significant. A stepped-wedge design with five steps, ten clusters and intracluster co-efficient of 0.15 and an average cluster size of 20 has a design effect of 0.40 (with only two baseline and one subsequent audit) (44). Using our expected sample size of 200 audit records from 10 services and a design effect of 0.4 with alpha = 0.05, an SD of 13.58, 99% power is achieved for detecting a 5% change in our primary outcome. This is a conservative estimate. This sample size also gives a statistically significant result if mean birthweight is 100 g higher after the intervention than in the pre-intervention state (e.g., 3.3 kg v 3.2 kg). For the proportion of pregnant women with their first antenatal visit prior to 13 weeks gestation, this study will produce a statistically significant result if the odds of a pregnant woman attending in the first trimester are 1.5 times higher in the PWG group than in the pre-intervention group.

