### Outcomes

The primary outcome measure is a change in the MCH Quality of Care Index (QCI) from aggregated de-identified health service audit data. The MCH QCI provides an indicator for overall adherence to delivering recommended services based on evidence based clinical best practice guidelines in the delivery of care. The MCH-QCI (%) is calculated from audit data as (total number of services provided)/(total number of recommended services) ^*^100 (Table 2) (41). Baseline audit data is collected from services at yearly intervals (over ~1 week at the end of each year) for the 5-year duration of the study. Given the stepped wedge start-time of the intervention, each service will have at least one set of pre-intervention audit data (some up to three) and at least two sets of post-intervention audit data (some up to four; Figure 1). Patients attending the services whose charts may be audited are women with an infant aged between 2 and 14 months at the time of audit, resident in the community for at least 6 months of the pregnancy and using the PHC service as her usual source of care.

**Table 2 T2:** Indicators included in MCH quality of care index.

Maternal Health QCI30 Clinical Indicators	Laboratory investigations: urinalysis (three time points), blood group, antibodies, full blood examination, rubella, Hepatitis B, syphilis serology, HIV, morphology US Physical examination: weight (two time points), body mass index; blood pressure (three time points); fundal height (two time points), fetal heart rate (two time points) History of risk factors: cigarette use, alcohol use, illicit drug use (each at two time points) Antenatal discussions: antenatal education, healthy living (nutrition, exercise, oral health, breastfeeding), psychosocial situation (domestic environment, family support, financial and housing)

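### The SD of 13.58 most naturally reads as the SD of service values but is used as the SD of one audit record, so the 99% power is not supported by the inputs as described

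*Protocol article*

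**What the plan says.** Three parts of the Protocol article bear on this.

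- **Sample Size, source of the SD:** "Actual mean of the MCH-QCI from 43 services previously involved with One21seventy MCH audits is 65.97% with standard deviation (SD) of 13.58" per cent. The number of services is given; the number of records behind the figure is not. The target is set by "a change of 5% is likely to be clinically significant".
- **Sample Size, use of the SD:** the design is described as "A stepped-wedge design with five steps, ten clusters and intracluster co-efficient of 0.15". Taking services to contribute about 20 records each, and counting two audits before the intervention and one after, the authors arrive at 0.40 as the design effect. They apply it to 200 records from the ten services. The result for the 5-point target reads "alpha = 0.05, an SD of 13.58, 99% power is achieved". The text goes on to call this estimate conservative.
- **Outcomes and analysis:** the primary outcome is "a change in the MCH Quality of Care Index (QCI) from aggregated de-identified health service audit data", computed as total services provided over total services recommended. The section on primary and secondary outcomes under Data Collection, Management and Analysis names the health service as the unit of analysis.

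**The concern.** A design effect built from an ICC and a cluster size multiplies the variance of a comparison of individual records. The SD that goes with it must therefore be the total SD of one record, between-service and within-service parts together. An SD across service values is a different quantity: averaging about 20 records removes most of the within-service part. At ICC 0.15 it is less than half the record SD.

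The source sentence, the aggregated definition of the index and the choice of unit all point to service values. The calculation treats the figure as record-level and describes no conversion. For services of 20 records, 13.58 could be both SDs only if the ICC were 1.

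The number of services is fixed at ten, so the power figure mainly governs how a result will be read. At 99% power, a null finding would be taken as strong evidence against a 5-point effect. At 44% it would not.

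**Working it through.** **Inputs** (all from Sample Size): SD 13.58; difference 5 points; ICC ρ = 0.15; k = 5 steps; b = 2 baseline audits; t = 1 audit after each step; n = 20 records per service; N = 200 records; α = 0.05. Sidedness is not stated there; I take two-sided.

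**1. Reproduce the design effect.** The standard stepped-wedge formula is

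DE = [1 + ρ(ktn + bn − 1)] / [1 + ρ(ktn/2 + bn − 1)] × 3(1 − ρ) / [2t(k − 1/k)]

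= (1 + 0.15 × 139) / (1 + 0.15 × 89) × 2.55 / 9.6 = 21.85/14.35 × 0.2656 = 0.404.

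This matches the stated 0.40.

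**2. Reproduce the power.** SE = SD × √(4 × DE/N) = 13.58 × √(4 × 0.40/200) = 1.215. Power = Φ(5/1.215 − 1.96) = 98.4%. One-sided it is 99.3%. The stated 99% therefore comes from using 13.58 as the SD of one record.

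**3. Read 13.58 as the SD of service values and keep ICC 0.15.** The variance of a service value based on 20 records is σ²[ρ + (1 − ρ)/n] = σ²(0.15 + 0.85/20) = 0.1925σ². So:

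- record SD σ = 13.58/√0.1925 = 30.95;
- SE = 30.95 × √(4 × 0.40/200) = 2.77;
- power = Φ(5/2.77 − 1.96) = 44%.

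A direct Hussey–Hughes variance (10 services, 5 steps, 7 audit rounds, 20 records per cell) gives 43.5%. The difference detectable with 80% power, (1.96 + 0.84) × SE, rises from 3.4 to 7.8 points.

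**4. The reverse check.** If 13.58 is the record SD, ICC 0.15 implies service values with an SD of 13.58 × √0.1925 = 5.96.

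**5. Sensitivity to the ICC.** Here 13.58 is held as the service-level SD, and σ and DE are recomputed for each ICC. At 0.15 the exact DE of 0.404 gives 43.5%, in place of 43.9% with 0.40.

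| ICC | Record SD | DE | SE | Power |
|---|---|---|---|---|
| 0.05 | 43.5 | 0.433 | 4.05 | 23% |
| 0.15 | 31.0 | 0.404 | 2.78 | 43% |
| 0.30 | 23.5 | 0.337 | 1.93 | 74% |
| 0.50 | 18.7 | 0.242 | 1.30 | 97% |

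**6. Sensitivity to records per service in the source data.** The article says audits range from under 5 to over 100 records. With ICC 0.15 and DE 0.40, source services averaging 5 records give σ = 24.0 and 64% power; averaging 100 they give σ = 34.1 and 37%.

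**The case against.** The strongest reply is that the article never says 13.58 is the SD of 43 service values. Records pooled over 43 services would also be described as coming from 43 services. The index is a ratio that can be worked out for one chart as well as for a whole audit. The sample size text itself pairs 13.58 with records, and on that footing its arithmetic is sound.

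A record SD near 13.58 is also plausible. With the 30 maternal indicators of Table 2, all assumed applicable and each met with probability 0.66, independence gives an SD of √(65.97 × 34.03/30) = 8.65. Reaching 13.58 needs an average inter-item correlation of about 0.05, whereas reaching 31 needs about 0.41. An SD of 31 is possible (the ceiling at this mean is about 47) but high.

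Finally, if 13.58 is service-level, the ICC may be the input that is wrong. The Design section argues for the stepped wedge where intra-cluster correlation is high, and a higher ICC restores much of the power.

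All of this stands as a limit on the size of the problem. It does not remove it. The record-level reading is only a possibility: nothing in the article states it, and the aggregated definition, the service as unit and the missing record count point the other way.

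A reader might infer that the trial's true power is 44%, or that the authors made an arithmetic slip. The documents support neither. The first needs both a service-level SD and an ICC of 0.15, and the second is refuted by steps 1 and 2. A reader might also carry the larger SD over to the annual audit calendar and quote a still lower power. That is a separate question, and it depends on how the services divide over one to three pre-intervention audits. This point does not rest on it.

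**Conclusion.** The point holds as a mismatch in the level of one input. On the most natural reading, an SD of service values is entered where the SD of a record is required. With the plan's own ICC, power for the 5-point target is then about 44%, against the stated 99%.

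The size is conditional. It assumes that 13.58 is service-level, that the source services averaged about 20 records, and that ICC 0.15 is kept. Changing only the ICC moves power from 23% (0.05) to 97% (0.50). If 13.58 is a pooled record SD, the figure stays at about 98%. What can be said without condition is that the inputs as described do not support the 99%, nor the claim that it is conservative.

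**What to change.** State in Sample Size whether 13.58 is the SD of service values or of individual records. From the 43-service audit data already cited, estimate the record-level SD and the ICC together, with the correlation between successive audits of the same service if the data allow. Recompute the design effect and power from that matched set, restate the figure, and remove the description of the estimate as conservative unless it still holds.

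The cost is a short re-analysis of existing data and a few revised sentences. No change to the design or data collection follows from this point alone. If 13.58 proves to be record-level, one sentence saying so closes the question of level.

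### The 99% power and design effect of 0.40 assume an audit after each of five steps; on an annual audit calendar power is about 53–70% or 80–90%, depending on which stated schedule holds

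*Protocol article*

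**What the plan says.** All references are to the protocol article.

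- **Sample Size, design:** the article states that its design "has a design effect of 0.40 (with only two baseline and one subsequent audit"). The layout to which this figure applies is described as "A stepped-wedge design with five steps, ten clusters and intracluster co-efficient of 0.15 and an average cluster size of 20".
- **Sample Size, power:** "Using our expected sample size of 200 audit records from 10 services", with a "design effect of 0.4 with alpha = 0.05, an SD of 13.58, 99% power is achieved for detecting a 5% change". The next sentence calls this estimate conservative.
- **Outcomes:** "Baseline audit data is collected from services at yearly intervals", in about one week at the end of each year over the five-year study. Each service is to have "at least one set of pre-intervention audit data (some up to three"), and two to four post-intervention sets.
- **Participant Timeline:** "two services commencing the intervention planning period at three monthly intervals". Allocation repeats the three-month steps.
- **Data Collection, Management and Analysis (Primary and Secondary Outcomes):** at least five audit sets per service. The analysis is a linear mixed model with a random community effect and fixed time effects, and an effect is expected 12 months after the start.

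**The concern.** A stepped-wedge design effect below 1 is earned by measuring between steps, so that at several time points some services are exposed and others are not. Five pairs starting three months apart all start within 12 months (0, 3, 6, 9 and 12). A yearly audit cannot fall after each step, so most pairs are indistinguishable in the audit data.

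The parenthesis in the sample size text also reads as three audits in total, with later audits as a bonus. In the design-effect formula the one subsequent audit is one per step, so the extra audits are already counted.

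If the stated power is wrong, a null result would be read as strong evidence against the women's groups from a study thought to miss a 5-point effect about 1% of the time.

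**Working it through.** **Inputs.** From Sample Size: SD 13.58, intracluster correlation ρ = 0.15, n = 20 records per audit, 10 services, effect 5 points, alpha 0.05. Sidedness is not stated; two-sided is assumed.

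**1. Reproduce the stated figure.** With k steps, b baseline audits and t audits after each step:

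DE = [1 + ρ(ktn + bn − 1)] / [1 + ρ(ktn/2 + bn − 1)] × 3(1 − ρ) / [2t(k − 1/k)]

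For k = 5, b = 2, t = 1: (21.85 / 14.35) × (2.55 / 9.6) = 0.4045, the stated 0.40. One baseline audit instead of two gives 0.441.

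Effective records: 200 / 0.40 = 500, or 250 per condition. SE = 13.58 × √(2/250) = 1.215. Power = Φ(5/1.215 − 1.96) = 98.4% (one-sided, 99.3%). The stated 99% is therefore reproduced closely.

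**2. What that layout contains.** b + kt = 2 + 5 × 1 = 7 audits per service, so 7 × 20 × 10 = 1,400 records. The 200 is the number per audit round. Generalised least squares with a random service effect and categorical audit periods on this seven-audit layout gives SE 1.221 and power 98.4%, which confirms the reading.

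**3. The calendar as written.** Put annual audits at months 0, 12, 24, 36 and 48, and starts at s, s+3, s+6, s+9 and s+12. For any s, one audit divides the services into two groups (2/8, 4/6, 6/4 or 8/2) that differ at that single audit. A third group can arise only if starts coincide with audits. Pre-intervention counts then differ between services by one, whereas Outcomes gives a range of one to three.

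**4. Power with two exposure patterns, five audits, categorical periods.**
- Sampling variance of a service's audit mean: 13.58² × 0.85 / 20 = 7.84.
- Between-service variance: 13.58² × 0.15 = 27.66.
- Variance of the audit that separates the groups, given the service's other four audits: 7.84 + (27.66 × 7.84)/(7.84 + 4 × 27.66) = 9.67.
- SE = √[9.67 × (1/a + 1/c)] for groups of a and c services.

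A common 12-month lag moves every service by one audit and leaves this unchanged.

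**5. Power with three patterns (one, two or three pre-intervention audits), same model.** Computed by generalised least squares over the possible splits of the five pairs.

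| Layout, five audits | SE | Power for 5 points | Detectable at 80% power (2.80 × SE) |
|---|---|---|---|
| Two patterns, 2/8 or 8/2 | 2.458 | 53% | 6.9 |
| Two patterns, 4/6 or 6/4 | 2.007 | 70% | 5.6 |
| Three patterns, 2/6/2 (lowest) | 1.791 | 80% | 5.0 |
| Three patterns, 4/2/4 (highest) | 1.544 | 90% | 4.3 |

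**6. Sensitivity.** A sixth audit gives 54–72% (two patterns) and 82–92% (three patterns). With five audits and a linear time term, power is about 87–95% across the layouts.

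**The case against.** The strongest reply is that 53–70% is not the only figure the article supports. Outcomes states one to three pre-intervention audits and cites Figure 1, which is not available here. Taken literally, those counts give three patterns and 80–90%. This stands: two stated inputs conflict, and the text alone does not settle which is right. A reader might infer that power simply is 53–70%, or that the audit counts under Outcomes are wrong. The documents do not establish either. Two points favour the lower range. The two to three years of implementation in Participant Timeline fit a one-year roll-out. Exact three-month steps can yield three patterns only in the borderline 2/6/2 case, at about 80%.

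Time coding is a second fair point. The article says only that time has fixed effects. A separate effect per audit is the usual reading and the one behind 0.40, but a linear trend would bring power to 87–95%. Leaving time out altogether would exceed 99%, but that contradicts the stated model.

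Third, five audits is a floor, so it is too firm to say that seven can never occur, though yearly audits over five years make it unlikely. More yearly audits would still not separate pairs that start between the same two audits.

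One might also push power lower by letting service means drift between audits. The article gives no between-audit correlation, so no such figure is relied on here.

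Finally, the plan to report estimates with 95% confidence intervals limits, but does not remove, the risk of misreading a null result.

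**Conclusion.** The point holds in this form: the 0.40 and the 99% belong to a seven-audit layout that an annual audit with three-month steps does not provide, and calling the estimate conservative is unsupported because 0.40 already counts all seven audits.

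On the stated inputs, the chance of missing a true 5-point change is about 30–47% if starts keep to three-month steps, and about 10–20% if the audit counts under Outcomes hold. A linear time term would make it about 5–13%. Every five-audit layout tried with a time effect falls below 99%.

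These figures assume a two-sided test, 13.58 as the total record-level SD, 20 records at every audit, constant within-service correlation and a normal approximation. A t-based test with ten services would lower them. The finding does not show that the trial is inadequate: on the counts under Outcomes, power is about 80% or more.

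**What to change.** 1. Reconcile the pre- and post-intervention audit counts in Outcomes with the three-month steps in Participant Timeline and Allocation, giving the count for each pair.
2. In Sample Size, replace the design effect and the 99% with a calculation on the actual audit dates and start dates. Use the planned time coding and the 12-month lag, and a sensitivity range for between-audit correlation, labelled as an assumption.
3. State the difference detectable with 80% power next to the 5 points regarded as clinically significant.
4. Delete the sentence that calls the estimate conservative.

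The cost is a recalculation, some rewording and a less favourable stated power. No extra services or records are needed.

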### Recruitment

Recruitment to this study is at three levels: PHC service recruitment, PWG facilitators and recruitment of individuals into the PWG.

#### PHC Services

An information sheet about the study and an invitation for services to self-nominate has been circulated through peak bodies, state health partners, investigators' networks. Follow up by meetings to provide further information and check eligibility has occurred with interested services. Attention has been paid to maximize variability amongst services as well as enabling services to make an informed choice about participation, considering all factors. Maximizing variability assists in determining how the intervention might be transferable to different settings. Service consent to participate involves meetings with the PHC service staff to discuss the study and written consent from an Aboriginal Community Controlled Health service Board or CEO to participate.

#### PWG Facilitators

Individuals are invited to participate as PWG Facilitators via the PHC health service. Members of the investigation team discuss the study with nominated PWG facilitators and seek written consent.

#### PWG Members

Individuals are invited to participate in the study via the PHC service and PWG facilitators. The PHC service determines the appropriate approach to recruitment depending on the context but includes activities: local advertisement, community meetings, via other local community groups and stakeholders. Interested individuals are provided information about the study and assessed for eligibility. Verbal and written consent to participate is obtained by the PWG facilitators. Within existing PWG groups, individuals who choose not to be part of the study will continue to participate in group activities outside of the MCH planning and implementation process.

PHC service and PWG retention are promoted by inviting PHC representatives and PWG facilitators to be members of the project steering committee. Regular email updates and newsletters are available to PHC service staff and PWG facilitators. In addition, a closed facebook group will be established so that they can share information and progress with each other. PWG participant retention is promoted by flexibility to the needs of the group when organizing planning and evaluation meetings; sharing newsletters and other study communications where appropriate; providing reminders of upcoming meetings and regular feedback on topics discussed.

Given the thorough processes that the services and investigator team undergo once services are involved it is unlikely that a service would withdraw. However, there is a plan in place if a service can no longer participate involving maximizing possible data collection for that service and adjusting the analysis accordingly. There may be changes in personnel at the PHC service and amongst the PWG facilitators. Comprehensive refresher training is available in any aspect of the study should PHC staff or PWG facilitators require this, managed within the pragmatic nature of the trial. Participants in the PWG may withdraw from the study for any reason at any time. If they choose to withdraw this will not affect their relationship with the PHC service or the investigator team. If they withdraw from the study they can request that data is returned or destroyed.

